### Study procedure

2.7

#### Data collection

2.7.1

All data collection will be conducted by the main researcher ([name]). An authorized optometrist will assist with the optometric assessment data collection. All vision-related assessment data will be collected at a local hospital in Norway. Data collection, including vision assessments and questionnaires, will take place at three or four time points, depending on group allocation (Fig. 1). Baseline evaluations include background demographics and vision function and cognitive assessment. Table 1 shows a detailed description of the assessment schedule for the three sub-studies.

#### Data handling

2.7.2

The electronic data capture (EDC) system InCRF will be used as the study database. Paper-based Case Record Forms (pCRFs) will be developed as templates to serve as the framework and reference for database development and to collect questionnaire information.

Data will be entered into electronic CRFs (eCRFs) in the InCRF study database in two ways.•On-site manual data entry from pCRFs and questionnaires•External data transfer for technical data from BulbiCAM examinations

Questionnaire data will be entered into the study database by [name]. Technical data from BulbiCAM examinations will be exported as encrypted files and subsequently imported into InCRF by a data manager (DM). Prior to study start, a data entry instruction (DEI) document will be made.

Participant identities in the database will be anonymized. Each participant will be assigned a unique study identification number, which will be stored in the database. The DM will be responsible for data validation of the eCRFs. In cases of missing data, logical inconsistencies, or interpretation issues, an electronic query (eQuery) will be issued through InCRF. Initial data validation will be performed by the DM once data from the first participant have been entered into InCRF. When all required participants have completed their final visit and the data entry have been completed in InCRF, the DM will perform the final data verification checks.

Screening analyses for logical errors will be performed on an ongoing basis, and any identified errors will be corrected after updated information is obtained from the site. When all detected errors have been resolved, the primary study database will be locked. The database will then be converted into a labeled SAS dataset, which will also be locked to prevent any changes or additions. In this SAS copy, the responsible statistician may create derived variables but may not correct or otherwise alter the original data.

If data corrections are required after database lock, the primary study database must be reopened and corrected in accordance with standard international procedures for database changes and documentation.

### Statistical methods

2.8

All participants fulfilling the inclusion and exclusion criteria, have given informed consent to participate and have started BCAM registration, are classified as included in the study. The participants classified as dropouts will be excluded from the statistical analysis. Descriptive analyses will be used to summarize the key characteristics of the participants. Categorical variables will be presented as frequencies and percentages, while means and standard deviations will be calculated for continuous and ordinal data. Randomization will be stratified by time since stroke onset and visual field loss using block randomization with varying block sizes, and these stratification factors will be accounted for in the analysis. Differences in age and sex will be considered in the analysis.

Continuously distributed variables will be presented as mean value with 95% confidence intervals. Standard deviation (SD) will be used as an expression of dispersion. Categorized variables will be given in classical contingency tables. Categorical variables will be analyzed by contingency table analysis. Intervention effects will be analyzed using ANOVA with repeated measurements. Depending on the initial analyses of the anonymized data, additional in-depth statistical analyses may be conducted to explore relationships between selected variables. Where appropriate, correlation and regression analyses will be performed. Data will be processed and analyzed using SAS software. For analysis of the qualitative data, as in sub-study III, all interviews will be audio-recorded, transcribed verbatim, and analyzed using thematic analysis according to Braun & Clarke [35].

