### Power analysis and sample size determination

2.4

A sample size power calculation was performed prior to the start of the study [33]. The power calculation serves as a lower-bound estimate of power if each patient has at least two measurements. Multiple observations per subject will increase the power and eliminate the impact of possible missing observations. With a significance level of 5%, a power of 90% and a Clinically Relevant Difference (CRD) of 1 x SD between groups A and B, at least 23 participants will be required in each group, with a total number of 46 participants. A total of 26 participants per group will be recruited to account for a 15% dropout, while retaining sufficient statistical power.

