**Fig. 2 fig2:**
[figure not shown]
Study randomization and stratification factors.

Within each strata the participants will be randomly allocated (1:1) to either immediate or delayed intervention at baseline. Allocation will be concealed in sealed envelopes prepared by an independent researcher. The main researcher will not gain access to the pre-randomization list.

Due to the nature of the intervention, neither participants nor the main researcher ([name]) can be blinded after allocation. Other project group members and researchers will be blinded to the treatment allocation.

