### Discontinuation/withdrawal

2.11

A participant may discontinue the study or withdraw their consent at any time without concerns about their future treatment or care. If a participant does not attend an agreed assessment/meeting, the researcher should try to motivate the participant to continue. If a participant decides not to continue for reasons documented as not being related to the research question, they will be classified as “dropouts” and replaced by a new participant. Reasons for discontinuation will be discussed in a dialogue between the lead researcher and the participant and subsequently evaluated by the research team in relation to the research questions. The dropouts will not be included in the statistical analysis. Participants who discontinue or exit the study for reasons related to the study question or to the study procedure or equipment will be classified as “patient withdrawals”. These will not be replaced, but they will be included in the analysis using a last observation-carried-forward procedure.

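### Randomised participants who stop for reasons judged unrelated to the research question are replaced and left out of the analysis, so the comparison is no longer protected by randomisation

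*Protocol article*

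**What the plan says.** Section 2.5 fixes when allocation happens: "Within each strata the participants will be randomly allocated (1:1) to either immediate or delayed intervention at baseline". Section 2.8 counts a person as included once they are eligible, have consented and have started the BulbiCAM registration, and then adds: "The participants classified as dropouts will be excluded from the statistical analysis".

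Section 2.11 sorts people who stop into two classes by reason:

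- **Dropouts** stop for reasons documented as unrelated to the research question. They are replaced, and "The dropouts will not be included in the statistical analysis".
- **Withdrawals** leave for reasons tied to the study question, procedure or equipment. They are not replaced and are analysed by LOCF.

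On who judges the reason, section 2.11 says: "Reasons for discontinuation will be discussed in a dialogue between the lead researcher and the participant and subsequently evaluated by the research team". Section 2.5 states that participants and the main researcher are unblinded after allocation and that other project members are blinded.

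Section 2.4 already enlarges the sample for losses: "A total of 26 participants per group will be recruited to account for a 15% dropout, while retaining sufficient statistical power".

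**The concern.** Whether a randomised person counts in the primary comparison depends on a judgement made after allocation. Section 2.11 does not confine the rule to people who leave before randomisation, and section 2.6 places randomisation directly after the baseline assessment, so most of the time at risk of stopping is after allocation.

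The two arms do different things during the eight weeks being compared. Group A trains for 20 minutes a day with weekly calls; group B waits on standard care. Fatigue, another illness or lack of time could plausibly be recorded as unrelated in either arm, yet arise at different rates and be associated with saccadic reaction time. If so, the people left in group A and in group B are no longer comparable groups, and a new recruit does not stand in for the person removed. At stake is the validity of the randomised estimate for the primary outcome.

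**Working it through.** **1. The plan's sample size, reproduced.** Inputs from section 2.4: "With a significance level of 5%, a power of 90% and a Clinically Relevant Difference (CRD) of 1 x SD between groups A and B"; two-sided testing is assumed because the section does not state sidedness.

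- Normal approximation: n = 2(1.960 + 1.282)² / 1² = 21.02, so 22 per group.
- Exact noncentral t: power is 89.97% at 22 and 91.2% at 23, so 23 is the smallest n that reaches 90%. This matches "at least 23 participants will be required in each group, with a total number of 46 participants". A one-sided test would give 18 and does not match.

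No stated figure is wrong on this point; the issue is who is analysed.

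**2. Is replacement needed for power?** With all 26 per arm contributing, power is 94.2%. With 15% lost, 26 × 0.85 = 22.1 per arm and power is about 90.0%. The planned 52 therefore covers the loss that the plan expects without replacing anyone.

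**3. Size of bias by simple algebra.** Score the outcome so that higher is better. Let a fraction f of one arm be excluded, with a mean d SD below that arm's mean, and nobody be excluded from the other.

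- Exclusion only: bias = f·d / (1 − f).
- Exclusion with replacement by people of average outcome: bias = f·d.
- With f = 0.15 and d = 0.25: 0.044 SD without replacement and 0.15 × 0.25 = 0.04 SD with it.
- With f = 0.15 and d = 1: 0.176 SD without replacement and 0.15 × 1 = 0.15 SD with it.
- With d = 0 (stopping unrelated to outcome): zero in both cases.

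Replacement restores the number analysed and shrinks the bias by the factor 1 − f. It does not remove it.

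**4. Simulation.** Assumptions, none of them in the article: no true effect, 26 per arm, baseline–week-8 correlation 0.6, baseline-adjusted analysis. The excluded are the lowest-ranked on the week-8 residual plus noise with SD 0.5 (strong selection), 1 (moderate) or 2 (weak). Four of 26 is 15.4%, close to the plan's 15%.

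| Excluded, A v B | Bias in SD (strong / moderate / weak) | Type I error |
|---|---|---|
| 4 v 0, no replacement | 0.18 / 0.14 / 0.08 | 13.4% / 9.4% / 6.4% |
| 4 v 0, with replacement | 0.16 / 0.11 / 0.07 | 11.5% / 8.8% / 6.3% |
| 4 v 3, no replacement | 0.04 / 0.03 / 0.01 | 7.7% / 6.2% / 5.0% |
| 4 v 4, no replacement | about 0 | 7.4% / 5.9% / 5.2% |

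Repeat runs move the bias by about 0.01 SD. The second row is the plan's own procedure. A ceiling for this kind of model, in which the four poorest outcomes in one arm are removed and replaced and a plain t-test is used, is 0.23 SD and 15.1%.

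**5. What changing the sentence alone achieves.** Someone who leaves before week 8 has only baseline data. Keeping such people with week-8 values predicted by regression on baseline left the bias unchanged in the 4 v 0 case (0.18 / 0.13 / 0.08 SD). Restoring them to the analysis set helps only as far as their week-8 outcome is collected.

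**The case against.** Several limits on this point are real.

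- **Who decides.** A reader might infer that the one unblinded researcher decides alone who is analysed. The article does not say that: the reason must be documented, and the research team evaluates it, its other members being blinded. That the lead researcher of section 2.11 is the main researcher of section 2.5 is a natural reading, but an inference. What stands is that the reason comes from an unblinded participant and may itself reveal the arm. Even a fully blinded judgement would not stop the arms from differing in how often and why people leave.
- **Direction.** A reader might infer that the rule favours the intervention by removing those who struggle with training. Section 2.11 keeps anyone who leaves for reasons tied to study procedure or equipment, and training burden plausibly falls there. A bias towards the intervention would need misreported or misclassified reasons, which the article does not show.
- **Size.** Four exclusions in one arm and none in the other is an assumption; the plan's 15% is an allowance across both groups. Near-balanced exclusion gives almost no bias.
- **Data.** Exclusion from analysis is not erasure. Section 2.7.2 bars changes to the locked data, so an all-randomised analysis of whatever was collected would remain possible.
- **Scope.** Some dropouts may leave before randomisation, where replacement is harmless. Section 3 also describes the findings as preliminary evidence.

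These points limit the claimed mechanism and size. None of them makes the rule safe. It is stated twice, so it is not a detail left to an analysis plan, and the article describes no analysis that restores the excluded people.

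**Conclusion.** The concern holds as a fault in the analysis set. The protocol removes randomised participants from the primary comparison, and replaces them, on a reason judged after allocation, in an open trial whose arms do different things at that time. Randomisation then no longer guarantees an unbiased comparison.

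Direction and size cannot be known from the article. Under the stated one-arm assumptions, with the planned replacement, bias is about 0.07 to 0.16 SD against a target difference of 1 SD, and type I error is about 6% to 12% rather than 5%. Bias is zero if exclusions are unrelated to outcome or selected equally in both arms. The bias is modest beside the target, but in the strong one-arm case the false-positive rate is more than doubled. Because this is the primary comparison and outcomes not collected cannot be recovered later, it should be settled before participants start to leave.

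**What to change.** 1. In sections 2.8 and 2.11, delete the exclusion of dropouts for anyone who has been randomised.
2. Analyse all randomised participants in their assigned arm with all observed data, using a likelihood-based repeated-measures model that retains incomplete cases. This replaces both the exclusion and the LOCF rule; leaving LOCF in place beside it would contradict it.
3. Keep inviting people who stop to the assessments already planned, above all week 8. Without this step the new wording recovers little.
4. If more people are recruited, they take the next envelope and are added; nobody randomised is removed. People who leave before randomisation may still be replaced.
5. Keep the reason for stopping as a descriptive variable.

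The cost is a wording change in two sections plus a small procedural one: continued contact with people who stop. There will be some missing data to model, and the estimated effect may be smaller. No increase beyond 52 is needed for the loss that the plan expects.

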### Outcome measures

2.9

The primary outcome is the change in the Saccadic Reaction Time (SRT), measured using the BulbiCAM visual field test [36]. SRT will be assessed at all measurement points throughout the study to evaluate both immediate and sustained effects of the vision rehabilitation training. Secondary outcomes include changes in occupational performance and satisfaction using the Canadian Occupational Performance Measure (COPM) [37,38], health-related quality of life (EQ-5D-5L) [39], Self-regulation Skills Interview [40], Brain Injury Associated Visual Impairment Impact Questionnaire (BIVI-IQ) [41], and a questionnaire on the impact of driving on daily life (IDDL). All will be evaluated at each measurement point. Additionally, changes in reading speed will be measured using the Norwegian version of the International Reading Speed Texts (IReST) [42] and visual functions will be assessed. In addition to these quantitative outcomes, qualitative data will be collected through semi-structured interviews to explore participants' experiences with vision loss, the impact of losing their driver's license on daily life and quality of life, and their expectations of vision rehabilitation before starting the home-based training and their perceptions of the vision rehabilitation after the eight weeks of training.

### Organization of data collection and data management

2.10

Data will be managed as recommended by the Norwegian Agency for Shared Services in Education and Research. Participants’ personal information will be stored on one of the devices that only the main researcher has exclusive access to. This computer is a separate PC where no other data is stored. All data from this test will be pseudoanonymized before use. Data recorded in the BulbiCAM will be registered with the participants project ID-numbers. All data from the electronic devices will be exported from the software to the InCRF database by an encrypted IRON-KEY. Data from the interviews will be collected by audio recording through either a digital platform (Zoom/Microsoft Teams) or physically with a Dictaphone through Nettskjema (nettskjema.uio.no) at a location chosen by the participant. Recordings of the interviews, transcription files and all other data will be stored pseudoanonymized on a research server. Paper-registered data will be temporarily stored in a locked cabin at the hospital research facility before being stored digitally on the research server. Data collection, breaks and the number of sessions, will be tailored to the individual participant to minimize fatigue.

### Discontinuation/withdrawal

2.11

A participant may discontinue the study or withdraw their consent at any time without concerns about their future treatment or care. If a participant does not attend an agreed assessment/meeting, the researcher should try to motivate the participant to continue. If a participant decides not to continue for reasons documented as not being related to the research question, they will be classified as “dropouts” and replaced by a new participant. Reasons for discontinuation will be discussed in a dialogue between the lead researcher and the participant and subsequently evaluated by the research team in relation to the research questions. The dropouts will not be included in the statistical analysis. Participants who discontinue or exit the study for reasons related to the study question or to the study procedure or equipment will be classified as “patient withdrawals”. These will not be replaced, but they will be included in the analysis using a last observation-carried-forward procedure.

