## Introduction

1

Stroke is a leading cause of acquired visual field loss (VFL) in adults. Each year, approximately 12,000 people suffer a stroke in Norway [1], and more than 60% experience post-stroke visual impairments, including VFL [2]. The Norwegian NOR-OCCIP study found VFL in 80% of patients two weeks post-stroke and in 55% after six months [3]. VFL significantly affects quality of life and daily functioning, including reading, driving, work, communication, and mobility [[4], [5], [6], [7], [8], [9], [10], [11]]. Revoked driving privileges due to VFL are a major concern for stroke survivors and are often associated with reduced independence, depression, and lower quality of life [8,[12], [13], [14]].

European and Norwegian stroke care guidelines recommend compensatory strategies for VFL [15,16], which may improve reading speed, daily activities, and overall rehabilitation outcomes [[17], [18], [19]]. Evidence suggests that systematic eye movement and search training can enhance saccadic efficiency and exploration, improving functional vision and subjective daily living [13,[20], [21], [22], [23]]. However, few patients can adopt these strategies independently [24], and vision rehabilitation is not routinely offered in Norway after stroke [11,25] due to low sensitivity of clinical tests, lack of standardized protocols, and limited knowledge about its effectiveness.

Standard visual field tests are static and do not assess functional vision or a patient's ability to compensate for VFL, creating uncertainty about fitness to drive [[26], [27], [28]]. Functional visual fields reflect how visual information is processed and utilized under dynamic, attention-demanding conditions. Such measurements can capture dimensions including the integration of peripheral vision, motion detection, and divided attention required for safe navigation in complex traffic environments [29,30]. Although functional visual field measures are expected to be more representative of real-world driving than static perimetry, no methods have yet been specifically developed for this purpose. However, eye movement perimetry provides several promising alternative objective metrics such as gaze behavior and saccadic reaction times, which may serve as proxies for functional visual field assessment [31,32].

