### Study design

2.1

The study will be performed as an open controlled and randomized stratified trial with a delayed-start design (Fig. 1). Participants will be randomized (1:1) to either an immediate (group A) or a delayed (group B) eight-week intervention. Both groups will perform objective and subjective assessments such as visual function assessments and questionnaires. Assessments will be performed at baseline, immediately after the intervention, and 12 weeks after the intervention. Participants assigned to the delayed group will begin the intervention with an eight-week delay.

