**Qualitative method**								
III	Individual interviews	Experiences	Researcher/participant	X	X	X		

a Only for group B.

Immediate group: Participants in the immediate group will receive the intervention immediately. The intervention consists of eight weeks of home-based training exercises for visual scanning, visual search and eye movements, aimed at developing compensatory strategies for visual field loss. The training will include both a licensed online vision training program (Vision Builder) [34] and manual exercises. Participants will be instructed to complete 20 min of vision training daily, with a minimum recommended total training of 20 h over the eight-week period.

Adherence, motivation and perceived visual function will be closely monitored throughout the intervention. Each participant will receive a short weekly telephone check-in with open-ended questions, and they will be asked to maintain a training diary. Adherence will be categorized as “good”, defined as performing vision training 5–7 days/week, as “partial”, performing vision training 1–3 days/week, or “none”, as no training. Active measures will be taken to promote compliance. Visual function assessments and questionnaires will be repeated immediately after the intervention in week eight, with a final follow-up assessment conducted 12 weeks after completion. Additionally, participants will evaluate the acceptability and relevance of the training through a survey and qualitative interviews.

Delayed group: Participants in the delayed-start group will serve as a waiting-list control group and receive standard care for the first eight weeks. After the waiting-list control period and corresponding assessments, they will receive the same vision rehabilitation intervention as described for the immediate group.

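### Carrying the last observation forward for patient withdrawals enters anyone who leaves before week 8 as zero change in SRT in the only randomised treated-versus-untreated comparison; the resulting bias can go either way

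*Protocol article*

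**What the plan says.** The protocol article, section 2.11, splits leavers into two classes. Those who leave for reasons unrelated to the research question are dropouts; they are replaced, and "The dropouts will not be included in the statistical analysis". The other class is "Participants who discontinue or exit the study for reasons related to the study question or to the study procedure or equipment". These patient withdrawals are not replaced, and "they will be included in the analysis using a last observation-carried-forward procedure".

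Section 2.9 defines the endpoint: "The primary outcome is the change in the Saccadic Reaction Time (SRT), measured using the BulbiCAM visual field test". Table 1 schedules it at weeks 0, 8, 16, 20 and 28, with nothing between weeks 0 and 8. Section 2.6 says that the delayed group "will serve as a waiting-list control group and receive standard care for the first eight weeks", after which it receives the same training.

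Section 2.8 names repeated-measures ANOVA for intervention effects. The article states no other missing-data method and no sensitivity analysis. Section 2.4 says of missing data: "Multiple observations per subject will increase the power and eliminate the impact of possible missing observations".

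**The concern.** Last observation carried forward (LOCF) assumes that nothing changes after the final attended visit. Here that assumption falls on the primary comparison. Group B is untreated only until week 8, so week 8 is the one point where randomisation compares training with no training. A participant in either arm who withdraws before then has only a baseline value. Carrying it forward fixes the change in SRT at zero, and the analysis counts that zero as a measurement.

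The rule is also reserved for exits connected with the study question, its procedures or its equipment. Missing values in this class are the more likely to be related to outcome.

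The reassurance in section 2.4 does not help. It depends on each patient having at least two measurements, and a participant who leaves before week 8 has one.

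A second effect concerns later visits. A group B participant who leaves during weeks 8 to 16 has an end-of-wait, untreated value carried into the post-intervention visits. That distorts the later description of group B but leaves the week-8 comparison alone, because the week-8 value was observed.

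At stake are the size of the primary estimate and the power of a 52-person trial.

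**Working it through.** **The plan's own figure.** With a difference of 1 SD, two-sided 5% and 90% power, the two-sample t-test needs 22.02 per group, so 23. This matches section 2.4. Power is 91.2% at 23 per group and 94.2% at 26.

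**Inputs**
- From the article: 26 per arm, effect d = 1 SD, no SRT assessment between weeks 0 and 8.
- Assumed, because the article does not give them: r, the improvement both arms share over eight weeks, from 0 to 0.5 SD; and wA and wB, the shares withdrawn before week 8 in groups A and B.

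Improvement in SRT is counted as positive.

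**Withdrawal unrelated to outcome.** Withdrawn participants contribute zero change, so

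estimate = (1 − wA)(r + d) − (1 − wB)r

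bias = −wA·d + r(wB − wA)

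| Withdrawn before week 8 (A / B) | d | r | Calculation of bias | LOCF estimate |
|---|---|---|---|---|
| 4 / 4 | 1 | any | −0.154 × 1 + r × 0 | 0.85 |
| 4 / 0 | 1 | 0.5 | −0.154 × 1 + 0.5 × (−0.154) = −0.231 | 0.77 |
| 6 / 2 | 1 | 0.5 | −0.231 × 1 + 0.5 × (−0.154) = −0.308 | 0.69 |
| 2 / 6 | 1 | 0.5 | −0.077 × 1 + 0.5 × 0.154 = 0 | 1.00 |
| 4 / 4 | 0 | any | 0 | 0 |
| 6 / 2 | 0 | 0.5 | 0.5 × (−0.154) = −0.077 | −0.08 |
| 2 / 6 | 0 | 0.5 | 0.5 × 0.154 = +0.077 | +0.08 |

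**Power and type I error, same mechanism.** These come from simulation with change-score SD 1 and 6,000 runs. At d = 1 and r = 0.5, LOCF power is 87% (4/4), 69% (6/2) and 96% (2/6). Using observed values only, it is about 90% in all three. At d = 0, LOCF type I error is 4.2% (4/4) and 5.7% (6/2 and 2/6).

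**Standard error.** With 4 leaving each arm, the mean LOCF standard error is 0.258 (d = 0) or 0.279 (d = 1). The 22 per arm actually measured support √(2/22) = 0.30. The LOCF figure is close to the estimator's own sampling spread (0.252 and 0.256). The interval is therefore not too narrow for what LOCF estimates. It looks more precise about the treatment effect than the measured data allow and, when there is bias, it is centred in the wrong place.

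**Withdrawal dependent on outcome.** Simulation with 26 per arm, baseline-to-week-8 correlation 0.6 and r = 0.5, where the 4 poorest improvers leave one arm:
- d = 0, they leave A: LOCF bias +0.13 SD.
- d = 0, they leave B: LOCF bias −0.12 SD.
- d = 1, they leave A: LOCF estimate 0.98 SD, so almost no shrinkage.

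For d = 0 the signs are the reverse of those under unrelated withdrawal.

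**The obvious replacement in the same setting.** With only baseline available before week 8, a missing-at-random model is close to a baseline-adjusted analysis of those measured. With d = 0 and the 4 poorest improvers leaving A, that analysis gives +0.20 SD and type I error of 15%, against +0.13 SD and about 8% for LOCF. With r = 0 the two biases are about equal, at +0.20 SD each.

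**The case against.** The strongest reply is that neither the size nor the direction of the bias can be read from the article, and that the standard replacement may do no better. Much of this stands.

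- **Recovery in both arms.** A reader might infer from the introduction, where a Norwegian cohort "found VFL in 80% of patients two weeks post-stroke and in 55% after six months", that both arms will improve while withdrawals stay frozen. That figure is prevalence of field loss, not SRT. It starts at two weeks, whereas training starts no earlier than four weeks post-stroke, and the strata reach beyond 12 months. Shared improvement is plausible for early entrants, but r = 0.5 SD is an assumption.
- **A fixed direction.** It is tempting to say that group A withdrawals shrink the effect and group B withdrawals inflate it. This holds only for withdrawal unrelated to outcome and, for group B, only with shared improvement. It can reverse when poor improvers leave.
- **The rate.** The 15% in section 2.4 is an allowance for dropout. By section 2.11 dropouts are excluded and replaced, so LOCF never applies to them. No rate is given for patient withdrawals.
- **False positives.** A marked rise in type I error needs an extreme case. With shared improvement of 0.5 SD, 30% leaving B and none leaving A gives 9.7%; at 15% it is 5.6%. Outcome-dependent withdrawal can also raise it.
- **Baseline freezing.** It applies only to exits before week 8.

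None of this supports keeping LOCF. With equal withdrawal unrelated to outcome, a real effect still shrinks by wA·d even with no recovery. Nor is the rule a detail left for an analysis plan, since section 2.11 states it outright.

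**Conclusion.** The point holds in a limited form. Section 2.11 fixes a rule that assigns zero change in the primary outcome to anyone withdrawing before week 8 and treats that value as data. For withdrawal unrelated to outcome, the assumed range (r from 0 to 0.5 SD; splits of 4/4, 6/2 and 2/6) gives a bias of −0.31 to 0 SD when the true effect is 1 SD, and −0.08 to +0.08 SD when there is none. When withdrawal depends on outcome the sign can reverse, so LOCF is not reliably conservative. The main damage is to the estimate and the power. The article does not support a claim of general type I error inflation, nor a claim that the bias favours a particular arm. Every size quoted rests on assumed withdrawal numbers and, except at 4/4 with unrelated withdrawal, on an assumed r.

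**What to change.** In section 2.11, replace LOCF with a likelihood-based repeated-measures mixed model using all observed SRT values, or with multiple imputation by arm using baseline SRT and the stratification factors. State that this primary analysis assumes data are missing at random. Align section 2.8 with it.

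In the same place, prespecify a delta-adjusted sensitivity analysis: shift the unobserved week-8 values of withdrawals over a stated range, separately in each arm, and report where the conclusion changes. This part is not optional, since the reasons that define a patient withdrawal are those under which missing at random may fail, and the primary analysis alone can then be as biased as LOCF or more.

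In section 2.4, remove the claim that repeated observations dispose of missing data.

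The cost is a few sentences, a little more analysis work in SAS, which is already the chosen software, and confidence intervals that reflect the missing data. The change should be made before database lock.
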